## Abstract

**Supplementary Information:**

The online version contains supplementary material available at 10.1186/s12954-025-01211-1.

## Introduction

More than 100,000 people died of an overdose in 2022 in the United States. The age-adjusted rate of overdose deaths almost quadrupled from 2002 to 2022, making overdoses one of the leading causes of injury death in adults. [1] Fentanyl and other illegally manufactured synthetic opioids drive overdoses and have contributed to historically high levels of death from overdose since 2014, starting in the East Coast and shifting to the West Coast in more recent years. This crisis has coincided with rapidly rising rates of hepatitis C virus infection, HIV outbreaks, and other sequelae of unsterile drug use. [2–4] The economic cost of the crisis exceeds $1 trillion annually. [5]

Persistently high levels of overdose in the United States have led to a call for new solutions. Overdose prevention centers (OPCs) have been proposed as a strategy to reduce drug-related harms in the context of a volatile illegal market dominated by highly lethal products. OPCs (also known as supervised consumption sites, safe injection facilities, drug consumption rooms, or harm reduction centers) are community-based facilities at which clients consume pre-obtained controlled substances under the supervision of personnel trained to intervene in the event of an overdose. [6] In most countries, OPCs resemble community health clinics, with booths that permit supervision by trained personnel. OPC staff also provide education about safer drug consumption practices, access to sterile supplies, referrals to other treatment, health, and recovery services. While OPCs have long been in operation in other countries, no publicly recognized OPCs existed in the United States before 2021. In July 2021, Rhode Island (RI) became the first state to authorize OPCs through legislation; the first OPC service will open in Fall 2024. [7] In November 2021, the first two publicly recognized OPCs in the US opened in New York City (NYC). [8–10]

Prior research from other countries suggests that OPCs have a variety of positive individual health and community-level outcomes. [11–15] The first sanctioned OPC opened in Switzerland in 1986, (16) and there are now > 200 sites in operation in 15 countries. [16] A study conducted in Vancouver showed that community overdose mortality decreased by 35% after the opening of an OPC, [17] while a study conducted in Toronto found a 67% reduction in the overdose mortality rate in neighborhoods after the opening of OPCs. [18] In Australia, emergency calls for suspected opioid overdoses declined significantly in the vicinity of an OPC after it opened. [19] Frequent OPC use has been associated with higher substance use disorder treatment initiation and uptake of other health and social services. [20–22] In France, OPC use was associated with a lower incidence of overdoses, abscesses, and emergency department visits, [23] resulting in 5–6 million euros of cost savings. [24] In the US, an evaluation of an unsanctioned OPC found that use of the site was associated with reduced syringe sharing, [25] fewer emergency room visits, [26] and improved syringe disposal. [25]

Despite this volume of evidence, there remain several critical unresolved questions pertinent to sanctioned OPC implementation in the US. First, as noted in a recent systematic review, [13] the majority of OPC research has involved sites located in Canada, France and Australia, which differ substantially from the US context. Domestic research is urgently needed, particularly in the era of unprecedented overdose rates driven by the fentanyl crisis. [27, 28] Moreover, differences in local drug markets, racialized policing practices, healthcare policy, wrap-around services, and the types of OPC service delivery models adopted may modify the effectiveness of OPCs relative to other countries, and thus warrant additional study. Second, while studies of the unauthorized US site are promising, its clandestine nature limits its scope of operations (and thus its impact). [29] Hence, the impact of sanctioned OPCs (serving a much larger and more diverse client population) on neighborhood-level outcomes warrants further study. Third, there are few, if any, comparative investigations of different OPC models, [30] despite facilities varying substantially in structure, cost, service provision, and scope. [16] Fourth, while a small number of cost-effectiveness analyses have been conducted for operational OPCs in other countries and for hypothetical OPCs in the US, [24, 31] almost all of these studies rely on programmatic cost estimates from a single OPC in Vancouver, Canada, and focus on HIV infections averted as the main outcome.

The planned and currently operational OPCs in NYC and RI offer an opportunity to address these gaps in our understanding of the effectiveness of OPCs in the United States. The two sites offer several interesting sources of contrast. First, they differ in the type of model adopted. OPCs in NYC follow two models: 1) medically supervised, in which licensed clinical staff are present to supervise overdose interventions and facilitate connections to care; and 2) peer supervised, in which trained peers are present to intervene in overdoses and refer clients to supportive services. In contrast, all OPCs in RI will follow the medically supervised model, and are required under state regulations to offer services for inhalation of controlled substances. [32] Second, the type of service setting in which OPCs are being implemented differs between the two jurisdictions. NYC OPCs are co-located in syringe service programs (SSPs), which provide a range of low-threshold health services (e.g., safer drug use supplies, HIV and hepatitis C testing, treatment referrals, clothing, nutrition, showers, and employment and housing referrals). All services available to SSP clients are available to OPC clients. Rhode Island’s first OPC will be co-located with an opioid treatment program. Third, the two sites offer geographic contrast, providing insights into the effects of implementing OPCs in a dense urban area (NYC, population size: 8.34 million) and in a small city (Providence, RI, population size: 189,563).

The Study Assessing the Effectiveness of Overdose Prevention Centers Through Evaluation Research (SAFER) aims to evaluate the effectiveness of the NYC and RI OPCs by conducting a parallel, multi-method, individual- and community-level evaluation of OPCs in NYC and RI in 2023–2027. By evaluating OPCs in these distinct contexts, SAFER intends to determine the generalizability of OPC effectiveness across diverse settings. The study aims include:*Identify individual health outcomes of OPC use* by investigating whether people who attend OPCs experience lower rates of fatal and non-fatal overdoses, drug-related health problems (e.g., skin & soft tissue infections), emergency department use, and a higher rate of initiating evidence-based treatment for substance use disorders, compared to people who use drugs and attend SSPs with no OPC.*Examine the community impact of OPCs* by determining whether census block groups surrounding OPCs experience a greater change in public health conditions (e.g., fatal and non-fatal overdoses), public disorder (e.g., drug-related litter, arrests, noise complaints), and acute economic conditions (e.g., property values) relative to a comparison set of census block groups unexposed to OPCs.*Investigate how operational contexts, program models, and operating procedures* shape how people who use drugs use OPCs and explore their impact on overdose vulnerability and other drug-related health outcomes, using qualitative and ethnographic methods.*Estimate OPC costs and potential cost savings to the healthcare and criminal justice systems associated with OPC use*, to support future estimation of longer-term cost and health outcomes.

## Materials and methods

### Theoretical framework

Our work is guided by the intersectional risk environment framework, [33] which draws attention to how structural (e.g., economic conditions), social (e.g., racism, stigma), and physical (e.g., availability of treatment programs) environments produce inequitable outcomes based on intersecting social identities (e.g., gender, race). By modifying the physical environment in which drugs are consumed and potentially attracting a new population who was not previously engaged in services, we hypothesize that OPC use will result in numerous health and social benefits to people who access them. Our framework guides survey development, data collection, and analytic strategies. The intersectional risk environmental framework also recognizes that people who use drugs (PWUD) are not only affected by their risk environments, but also interact with and influence it. Hence, we hypothesize that communities in which OPCs are located will experience public health, public safety, and economic benefits by increasing health, treatment, and social services engagement among PWUD. Finally, the framework acknowledges that PWUD differentially experience socio-economic marginalization and social discrimination, which produces inequitable patterns of service engagement based on social positions. Thus, in our qualitative work, we adopt ethno-epidemiological methods [34] to understand how operational contexts, program models, and operating procedures influence program effectiveness for sub-populations of PWUD (e.g., women, racialized PWUD), including in relation to key outcomes. A summary of our aims, approach, and the timeline for data collection activities is shown in Fig. 1. Methods are described below by study aim.

**Fig. 1 Fig1:**
[figure not shown]
Summary of study aims and timeline for data collection/assessments

### Aim 1: Individual health and treatment outcomes associated with OPC use among PWUD

#### Study design

While a randomized controlled trial (RCT) would be the gold standard for OPC evaluation, community and political factors that drive the timing of OPC service openings make randomization unfeasible, and RCTs of OPCs have previously been deemed unethical due to a lack of equipoise. [35] Hence, we use a quasi-experimental, pre-/post-intervention design with a comparison group, [36] to test whether individuals who use an OPC experience greater changes in the outcomes of interest than individuals who do not use an OPC. We recruit participants from two types of organizations that serve similar populations, facilitating group comparability by level of OPC use: (1) harm reduction organizations that provide OPC services (two sites in NYC) or plan to provide OPC services (one site in RI); and (2) a comparison set of SSPs with no plans to open an OPC (five organizations in NYC and three in RI). The target sample is 250 in each arm per jurisdiction, so that we recruit 500 participants in NYC and 500 in RI (N = 1000 total). Target numbers per site are proportional to the client population served by each organization. We collect pre- and post-OPC data from all study participants, including administrative health records and survey data, as described below.

We use venue-based recruitment for two reasons. First, this ensures that all groups represent a comparable underlying population of individuals already connected to a harm reduction service provider. Second, this permits us to compare populations that receive harm reduction services (e.g., syringe exchange, naloxone), so we can isolate the effect of OPC use on outcomes.

To be eligible for the study, participants must have used an illegal drug in the past 30 days. Further, they must be ≥ 18 years old and active clients of an OPC and/or SSP, defined as use in the past 30 days. They must be able to complete a survey in English or Spanish and provide written informed consent. Inclusion criteria for participants recruited at an OPC site also include use of the OPC service in the past 30 days. Study participants complete 60–90-min, in-person, computer-assisted surveys with a trained interviewer at baseline and months 6, 12, and 18. While initial recruitment takes place at the OPCs and SSPs, later in-person interviews take place at the OPC/SSP, at a field office, or a participant’s chosen location. In addition, they are recontacted each month (in person or by phone) during the 18-month period for a 5–10-min check-in.

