#### Outcomes measured through administrative health records

To provide a comprehensive assessment of change in health conditions associated with OPC use, we complement self-reports with administrative health records. Participant identifiers will link participants to their administrative health records. Table 2 presents the sources and types of information we plan to collect, leveraging our partnerships with the NYC Department of Health and Mental Hygiene (DOHMH), NYS Office of Addiction Services and Supports (OASAS), the RI Department of Behavioral Health, Developmental Disabilities, and Hospitals (BHDDH), and the Rhode Island Department of Health (RIDOH). We link participants to their health records 18 months prior to their first survey date and for up to three years post-enrollment, to track pre- and post-OPC changes in their health using probabilistic matching with the last four digits of each participants’ social security number, first and last name, date of birth, and sex. [42] We use a minimum, common set of data sources, including Medical Examiner, Medicaid, and data from licensed substance use disorder treatment facilities (through OASAS and BHDDH), ensuring a high degree of comparability across jurisdictions. In Rhode Island, we can also link participants to prescription drug monitoring program data, as we have done in prior work. [43]

**Table 2 Tab2:** Administrative health record data sources linked with study participants

Domain	Items	NYC data^1^	Rhode Island data^2^
Fatal overdose	All drug overdose, stimulant, and opioid	Office of Chief Medical Examiner	Office of Chief Medical Examiner
Non-fatal overdose	All drug overdose, stimulant, and opioid	NYC Regional Health Information Exchange (RHIO), Statewide Planning and Research Cooperative System (SPARCS),^3^ Medicaid	Emergency medical services data, Medicaid^4^
Drug-related health conditions	Hepatitis C, HIV, skin and soft-tissue infections, infective endocarditis	NYC RHIO, SPARCS, and Medicaid	Medicaid^4^
Emergency department visits	Overall ED use, drug-related emergency department (ED) visits	NYC RHIO, SPARCS, and Medicaid	Medicaid^4^
Substance use disorder treatment	Initiation in a licensed treatment program, including medications for OUD	OASAS and Medicaid	Prescription drug monitoring program, BHDDH, and Medicaid

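### People recruited at an operating OPC have already used it, so Aim 1 cannot have pre-OPC data on every participant: they have no pre-OPC baseline survey, and only recent starters have pre-OPC records

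*Protocol article*

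**What the plan says.** The Aim 1 Study design section says "we use a quasi-experimental, pre-/post-intervention design with a comparison group" and sets out to test whether OPC users change more than non-users. It then states: "We collect pre- and post-OPC data from all study participants, including administrative health records and survey data". Survey data are therefore explicitly part of the claim.

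The eligibility paragraph of that section adds: "Inclusion criteria for participants recruited at an OPC site also include use of the OPC service in the past 30 days". The section on administrative health records says: "We link participants to their health records 18 months prior to their first survey date and for up to three years post-enrollment". It gives the tracking of change from before to after OPC use as the purpose of this linkage.

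The dates are in the Introduction. For NYC: "In November 2021, the first two publicly recognized OPCs in the US opened in New York City". For RI: "the first OPC service will open in Fall 2024". The study is an "individual- and community-level evaluation of OPCs in NYC and RI in 2023–2027". The RI recruitment site is described as an organization that plans to offer an OPC, not one that already does.

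The Aim 1 Analyses section takes past-month OPC use, updated over time, as the exposure. It fits marginal structural Cox models whose weights condition on the exposure history and on confounders that include earlier non-fatal overdose and healthcare use.

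**The concern.** The entry rule and the data claim cannot both be true for people recruited at an operating OPC. Their first interview comes after at least one OPC visit, so no survey wave precedes exposure. The record look-back is tied to the interview date and not to first OPC use, so the part of it that is truly pre-OPC shrinks the longer a person has been attending.

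Three things are at stake.

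- **The design claim.** For part of the OPC arm, the period treated as before is partly or wholly exposed.
- **Confounder adjustment.** For someone already using the OPC at entry, prior overdose and healthcare use may partly result from earlier OPC use. Weighting on them as baseline confounders can then remove part of the effect being estimated.
- **Selection.** People who began using an OPC and then died or stopped attending before enrollment cannot enter the OPC arm. This matters most for fatal overdose, the first hypothesis listed.

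The limitations in the Discussion cover non-randomization, the small number of OPCs and loss to follow-up. They do not mention OPC use before enrollment.

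**Working it through.** **Inputs.** 250 per arm per jurisdiction (Study design); OPC use within 30 days before entry for OPC-site recruits (Study design); look-back of 18 months from first survey (administrative records section); NYC opening November 2021 and RI opening Fall 2024 (Introduction); study period 2023–2027 (Introduction). Enrollment months are not in the text, and the timeline figure is not available.

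**Step 1, sample.** 250 × 2 arms × 2 jurisdictions = 1000, which matches the stated total.

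**Step 2, baseline survey.** The interview follows OPC use for all 250 NYC OPC-arm recruits. If the rule also governs the RI host site, the number is 250 + 250 = 500 of 1000.

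**Step 3, pre-OPC time per person.** Let d be the months from a person's first OPC use to the first survey. Pre-OPC record months = max(0, 18 − d). For survey items with 6-month recall, pre-OPC months = max(0, 6 − d).

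| d (months) | Record months before OPC use | Months within 6-month recall |
|---|---|---|
| 1 | 17 | 5 |
| 3 | 15 | 3 |
| 6 | 12 | 0 |
| 12 | 6 | 0 |
| 15 | 3 | 0 |
| 18 or more | 0 | 0 |

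**Step 4, what the opening dates imply.** Nobody can have used these sites before they opened, so the opening date caps d and gives a minimum for pre-OPC record time.

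- NYC: November 2021 + 18 months = May 2023. A January 2023 enrollee has d of at most 14, so at least 18 − 14 = 4 pre-OPC months. From May 2023 on, the guaranteed minimum is 0, and the actual figure depends on when that person started.
- RI: a person enrolled 1, 6 or 12 months after opening has at least 17, 12 or 6 pre-OPC months. From 18 months after opening, the minimum is 0.

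**Step 5, can the look-back be split?** Dividing it into before and after requires each person's first-use date. Table 1 lists OPC use for the past 30 days only. The item on year and month of first use appears under harm reduction services generally. The monthly check-ins only run forward from enrollment, and none of the record sources in Table 2 is an OPC attendance record. On the items listed, OPC use earlier than 30 days before baseline is unobserved, although the weights are meant to condition on the full exposure history.

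**Step 6, RI.** The Study design section recruits at a host that is still planning its OPC. Before opening, nobody there can meet the 30-day rule if the host counts as an OPC site. If it does not count, people recruited before opening have true pre-OPC baselines. The two statements need reconciling.

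**The case against.** The strongest reply is that much pre-OPC information does exist and that the analysis is not a simple before/after comparison.

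- **Records.** The look-back was designed to reach before OPC use. Anyone who started less than 18 months before baseline has pre-OPC records, up to about 17 months. Survey items with 6-month or lifetime recall can also reach back for recent starters. This stands. A reader might infer that pre-OPC data are absent altogether, and the documents do not support that.
- **Site opening is not personal first use.** A reader might infer that NYC windows starting after November 2021 hold no pre-OPC time, or that a January 2023 enrollee has at most 4 of 18 usable months. Neither follows. A client who first attended one month before a 2024 baseline has about 17 unexposed months, and the 4 months are a minimum for the individual. The NYC sample also includes 250 people recruited at syringe service programs (SSPs), who need not have used an OPC.
- **Time-updated exposure.** Starts, stops and restarts all contribute, including SSP recruits who begin OPC use, so Aim 1 as a whole is not a prevalent-user comparison. Marginal structural models are also built for confounders affected by earlier exposure. This stands for exposure observed during follow-up. It does not cover use before enrollment that the listed items do not capture.
- **Selection.** SSP recruits must also be current clients, so both arms consist of people still attending. But only in the OPC arm does that selection come after the exposure of interest has begun.
- **First-use date.** Table 1 is a summary, and the full instrument is in an appendix not available here. It may already ask for this date, so its absence cannot be asserted.

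**Conclusion.** The statement that every participant contributes data from before and after OPC use, surveys included, is wrong. No one recruited at an operating OPC has a pre-OPC baseline interview. This is certain for the 250 NYC OPC-arm recruits and extends to as many as 500 of 1000 if the rule applies at the RI host. Pre-OPC records exist for those who started less than 18 months before baseline, and not for those with 18 or more months of use. How many fall in each group cannot be worked out, because neither enrollment months nor time since first use is given.

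For prevalent users at entry, baseline confounders may partly reflect earlier OPC use, and early deaths and drop-outs are missing from the arm. The planned models reduce this problem but do not remove it. The two mechanisms can act in opposite directions, so the net direction of bias is unknown. A reader might be tempted to put a figure on it by diluting an assumed rate ratio by the exposed share of the before period. That would describe an uncontrolled before/after estimator, not the marginal structural Cox model planned here, and the documents give no basis for a number.

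**What to change.** 1. Correct the Study design statement: OPC-site recruits have no pre-OPC survey, and pre-OPC records are available only for those who started within the look-back.
2. Reconcile the description of the RI host as a planned site with the 30-day use rule, stating whether people may be enrolled there before opening.
3. Make sure month and year of first OPC use are recorded at baseline for all participants, SSP recruits included. If the appended instrument already asks this, say so and use it.
4. For those with OPC use before enrollment, request records from 18 months before first use. The look-back from the first survey becomes d + 18 months. The earliest NYC date is November 2021 − 18 months = May 2020.
5. Take baseline confounders from before first use where records allow, and include pre-enrollment OPC use in the exposure history behind the weights.
6. Pre-specify an analysis that separates new users (SSP recruits who start OPC use, RI first users) from prevalent users. It need not replace the main estimate, since making it primary would trade away precision and the number of new users is unknown.

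The cost is a longer linkage request, at most one survey item, and some analysis text. The new-user estimate will be less precise. The date item and linkage window should be settled early, because a start date missed at baseline is hard to recover.
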